#### Secondary outcomes

Secondary outcomes include: (1) the PSV, EDV, RI, and diameter of the CCA and VA at T0, T2, T3, and T4; (2) the rate of ptosis and conjunctival flushing at T1 and T3 (ptosis and conjunctival flushing are considered the standard indicators of SGB of success [25]); (3) the numerical rating scale (NRS) at T0 and T4. The NRS allows the patient to describe the intensity of his/her pain as a number, usually ranging from 0 to 10, where 0 means no pain and 10 means pain as “bad as it could be” [26].

Adverse events (AEs) or serious adverse events (SAEs) will be collected at each assessment time point and any AEs or SAEs related to the intervention will be reported. For an overview of the schedule of enrolment, interventions, and assessments please see Fig. 2.

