**Methods:**

A randomized controlled crossover trial with 38 participants will be conducted. Participants who have primary headaches will be assigned to either group A or B. Patients in group A will receive SGB with 6 ml 1% lidocaine, and after a one-week washout period, they will undergo the second SGB with 6 ml normal saline. In contrast, patients in group B will receive the opposite protocol. Data will be collected at baseline (T0) and at 15 min after the first intervention (T1), 15 min before the second intervention (T2), 15 min after the second intervention (T3) and at a 3-week follow up (T4). T1 is the primary time point for the primary outcome analysis. The primary outcomes include the peak systolic velocity (PSV), the end diastolic velocity (EDV), resistance index (RI) and vessel diameter of the common carotid artery (CCA) and vertebral artery (VA). The secondary outcomes include the rate of ptosis, the rate of conjunctival flushing, and the numerical rating scale (NRS) pain score. Additionally, adverse events (AEs) or serious adverse events (SAEs) will be collected at each assessment point.

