**Discussion:**

This study will comprehensively investigate the efficacy of SGB in extracerebral blood flow. Our research may also suggest that SGB will be effective in reducing pain in patients with primary headaches.

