### Trial design

A double-blinded, randomized controlled crossover trial will be conducted, and all subjects will undergo ultrasound-guided SBG. Group A will first undergo SGB with 6 ml 1% lidocaine. After a one-week washout period, this group will receive ultrasound-guided SGB with 6 ml normal saline. In contrast, group B will receive the opposite protocol. That is, group B subjects will first receive SGB with 6 ml normal saline, and after a one-week washout period, this group will receive SGB with 6 ml 1% lidocaine.

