### Intervention

All participants will undergo two SGBs, with a one-week washout period between them. For the ultrasound-guided SGB, each patient will receive 6 mL 1% lidocaine and 6 mL normal saline at one-week intervals to allow a washout period for the injection. The 1% lidocaine is composed of 2% lidocaine and normal saline in a 1:1 ratio (for example, the 1% lidocaine 2 mL is prepared by combining 2% lidocaine 1 mL, and normal saline 1 mL) [18, 19].

The patients will be positioned in a supine position with their neck slightly hyperextended. Prior to the procedure, the C7 level is confirmed by the use of a 7–14 MHz linear probe (S-Nerve, Sonosite, USA). On the short-axis view, the posterior tubercle and the vertebral body show as a slope in the transverse process of C7. Sonoanatomy of the neck at the C7 level is confirmed by the absence of the anterior tubercle. The thyroid, inferior thyroid artery, oesophagus, internal jugular vein, CCA, VA, and prevertebral fascia are also confirmed. Colour Doppler imaging is utilised to avoid penetrating the CCA, VA, and the internal jugular vein during the needle insertion. The neck area will be sterilised and the probe will be covered with sterilised vinyl. At the C7 level, the probe will be placed at the anterior scalene muscle, which is located between the carotid sheath and the brachial plexus. A 25-gauge, 6-cm needle will be inserted laterally, 5 mm from the probe. The needle tip is placed posterior to the carotid artery and anterior to the longus colli muscle under the transverse short axis for the in-plane approach. The assigned dosage of 1% lidocaine or normal saline will be injected in the patients.

At the end of the SGB, another doctor, who is not involved in the operation, will observe the ptosis and conjunctival flushing. Before and 15 min after the SGB, the flow measurements will be recorded by an ultrasound specialist. Sonograms will be obtained with a Mylab 90 (Genova, Italy) by using a linear probe (curved-array transducer, CA431, 1–8 MHz).

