### Data collection process

We will confirm eligibility criteria are met through review of the participant’s medical records. The following data will be collected for each participant: patient identifiers and demographic information, study intervention details, and the peak systolic velocity, vessel diameter, and RI of the CCA and VA, as measured at T0, T1, T2, T3, and T4. The rate of ptosis and conjunctival flushing will be measured at T1 and T3; the pain scores will also be recorded at T0 and T4.

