### Monitoring of data quality

The peak systolic velocity, vessel diameter, and RI of the CCA and VA will be detected by an ultrasound specialist using the same ultrasound instrument. The rate of ptosis and conjunctival flushing will be recorded by a doctor. Another pain physician will teach patients to use the NRS scoring system and then record pain scores. Data are directly recorded in the electronic study database, which is backed up regularly. All of the assessors will be blinded from the information linking participants and interventions. Study participation will last 3 weeks from enrolment for each participant. No interim analysis will be performed during the study.

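### Pain is scored only before any block and after both, so the trial cannot support a controlled statement that the block reduces headache pain

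*Protocol article*

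**What the plan says.** The Secondary outcomes section places the pain score at two times: "the numerical rating scale (NRS) at T0 and T4". The Data collection process section agrees: "the pain scores will also be recorded at T0 and T4". The Objective mentions pain scores without giving a time. The schedule figure is not reproduced in the text at hand, but the two sections that do give times match.

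The Methods part of the abstract puts the last two assessments at "15 min after the second intervention (T3) and at a 3-week follow up (T4"), so T4 follows the second injection. The Intervention section states: "All participants will undergo two SGBs, with a one-week washout period between them". Under Trial design, group A starts with lidocaine and then: "After a one-week washout period, this group will receive ultrasound-guided SGB with 6 ml normal saline". Group B has the reverse order. Monitoring of data quality adds: "Study participation will last 3 weeks from enrolment for each participant".

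On what pain data are expected to show, the abstract says: "Our research may also suggest that SGB will be effective in reducing pain in patients with primary headaches". The main Discussion goes further. It makes observing the block's efficacy in headache patients part of the study's purpose, and it anticipates that the block will ease their pain.

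**The concern.** A placebo-controlled crossover separates drug from placebo only through measurements taken while the two groups differ in what they have received. For blood flow the plan has these at T1 and again at T3. For pain it has none, because the NRS skips T1, T2 and T3.

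Primary headache fluctuates, and patients approached in a pain centre may enter at a bad time. A fall in the NRS over three weeks can therefore arise from natural course, regression to the mean or expectation. If such a fall is reported from a double-blind randomised trial alongside the efficacy wording, readers will tend to grant it a placebo control that it does not have. An analysis plan cannot repair this later, because the scores it would need are not collected.

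**Working it through.** **No plan figure to reproduce.** The Sample size section concerns peak systolic velocity only, and the article gives no mean, SD or expected change for the NRS. Every NRS value below is an assumption.

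**Step 1: exposure at each assessment** (Trial design, Intervention, abstract Methods).

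| Time | Group A has had | Group B has had | NRS taken? |
|---|---|---|---|
| T0 | nothing | nothing | yes |
| T1, T2 | lidocaine | saline | no |
| T3 | lidocaine, then saline | saline, then lidocaine | no |
| T4 | both | both | yes |

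Only two NRS contrasts are possible: A against B at T4 (adjusted for T0 or as change from T0), and the change from T0 to T4 with the groups pooled.

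**Step 2: A against B at T4.** Put the blocks at weeks 0 and 1 and T4 at week 3, following the stated three weeks from enrolment. Lidocaine was then given about 3 weeks earlier in A and about 2 weeks earlier in B. Assume a lidocaine effect of τ points, of which a fraction r is retained each week, and no lasting effect of saline. The expected difference in retained effect is

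D = τ(r³ − r²).

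- r = 1 (full persistence): D = 0.
- r = 0 (effect gone): D = 0.
- τ = 3, r = 0.75: D = 3 × (0.4219 − 0.5625) = −0.42.
- The largest size is at r = 2/3: D = 3 × (8/27 − 12/27) = −12/27 = −0.44.

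For τ from 1 to 3, SD 2 to 2.5 and 17 per group, the two-sided t-test at 0.05 has power of about 5% to 10%, close to the significance level itself. If T4 is instead counted from the second block, the intervals are 4 and 3 weeks. The largest size is then smaller: 3 × (0.75³ − 0.75⁴) = 3 × 0.1055 = 0.32.

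**Step 3: pooled T0 to T4 change.** Suppose lidocaine has no effect and the NRS falls by m points from natural course or placebo response. With n = 34 (2 × 17 completers), the noncentrality is m/(SD/√34), where √34 = 5.83. Probabilities are from the one-sample t-test, two-sided at 0.05.

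| Fall m | SD of change | m/(SD/√34) | P(significant) |
|---|---|---|---|
| 0.5 | 2.5 | 1.17 | 0.20 |
| 0.5 | 2.0 | 1.46 | 0.29 |
| 1.0 | 2.5 | 2.33 | 0.62 |
| 1.0 | 2.0 | 2.92 | 0.81 |
| 1.5 | 2.5 | 3.50 | 0.92 |
| 1.5 | 2.0 | 4.37 | 0.99 |

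The spread shows how strongly the result depends on the assumed fall. Every row exceeds 0.05, and in none of them does significance say anything about lidocaine.

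**The case against.** The strongest reply is one of proportion. Pain is the last of three secondary outcomes. The stated objective is cervical blood flow, the primary outcomes are Doppler measures at T1, and the sample size rests on carotid velocity. None of these depends on the NRS. The abstract sentence is hedged, and the article specifies no analysis particular to the NRS, so misattribution is foreseeable but not planned. This stands, and it limits the severity.

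Three stronger readings are tempting, and the documents do not support them.

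- A reader might infer that the trial can say nothing about pain. It can describe the change from T0 to T4; it cannot attribute that change to the block.
- A reader might infer that the T4 group comparison contains no information at all. Under partial decay of an effect it contains a little, as Step 2 shows. It is exactly zero only if the effect fully persists or has fully gone.
- A reader might infer that a false positive is nearly certain. Only the larger assumed falls give that, and the article supplies no figure to choose among them.

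The hedged abstract does not remove the point, because the main Discussion names efficacy in headache patients as part of the purpose. Nor is this a detail left to a fuller document: the article fixes the pain time points twice.

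**Conclusion.** The point holds for controlled or causal statements. With the NRS at T0 and T4 only, the trial cannot separate lidocaine from saline, natural course or expectation as the cause of a change in pain. This conclusion rests only on the stated measurement times and on the fact that everyone receives both injections. The sizes given (a group difference of at most about 0.44 points, power of about 5% to 10%, and a probability of about 0.20 to 0.99 of a significant uncontrolled fall) rest on assumed NRS values and illustrate it.

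Severity: should be fixed. The randomised blood-flow comparison at T1 is untouched, so it would be wrong to read this as a flaw in the trial's main question.

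**What to change.** 1. State that the T0 to T4 change in NRS is descriptive only, and remove the pain-efficacy wording from the Discussion part of the abstract and from the main Discussion. This is the essential part; it is editorial and costs nothing. It should apply to the whole article, since wording cannot be limited to a subset of patients.
2. For participants still to be enrolled, also record the NRS at the existing T1, T2 and T3 contacts. Name T2, adjusted for T0, as the placebo-controlled pain comparison. T3 gives a lidocaine against saline contrast only within the crossover and only if there is no carry-over, and this should be said.

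The cost of the second change is one 0 to 10 question at each of three visits that already take place. Its yield is limited: Trial status reports 27 of 38 enrolled by 12 October 2017, which leaves at most about 38 − 27 = 11 patients. That comparison should be labelled exploratory.

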### Sample size

The sample size was calculated based on the CCA blood flow results reported previously [11]. With an expected difference of 10 cm/s in peak systolic velocity of the CCA between group means, an SD of 10 cm/s, α = 0.05, and β = 0.8, a sample size of 17 patients was required in each group. To compensate for a dropout rate of up to 10%, we will enrol a total of 38 cases (19 for each group) for this study. Although the study is powered to allow a 15% dropout rate, we will make every effort to minimise patient loss and missing data during the trial period.

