### Blinding

The participants, researchers, and outcome assessors will remain blind to group allocation throughout the study. Participants will be assigned codes and will be concealed during the allocation process to ensure proper blinding. The researchers responsible for performing the intervention and evaluating the outcomes will not know the study design, allocation, objectives, or expected outcomes.

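### The reporting commitment for adverse events is tied to relatedness; a saline-controlled crossover should report all collected events by treatment received (minor point)

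*Protocol article*

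**What the plan says.** The article speaks of adverse events in two places.

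- The Methods paragraph of the Abstract says that "adverse events (AEs) or serious adverse events (SAEs) will be collected at each assessment point". It has no relatedness condition and no reporting rule.
- The Secondary outcomes section repeats the collection ("Adverse events (AEs) or serious adverse events (SAEs) will be collected at each assessment time point") and then, in the same sentence, gives the reporting commitment: "any AEs or SAEs related to the intervention will be reported".

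Adverse events are not among the three numbered secondary outcomes, and the Statistical analyses section describes no analysis of them. Nothing else in the article promises to report events that are not judged related.

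Two other statements bear on the relatedness judgement. The Secondary outcomes section notes that "ptosis and conjunctival flushing are considered the standard indicators of SGB of success". The Blinding section states that "The participants, researchers, and outcome assessors will remain blind to group allocation throughout the study", and Monitoring of data quality adds that "All of the assessors will be blinded from the information linking participants and interventions".

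**The concern.** Collection is unconditional and reporting is conditional. The condition has work to do only if reporting is meant to be narrower than collection, so on its natural reading the sentence lets events judged unrelated drop out of the report.

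In an uncontrolled series a causality judgement may be the only way to separate effects of treatment from background events. Here each patient is to receive both lidocaine and saline through the same needle procedure, in randomised order. Counting all events by treatment received shows what lidocaine adds without anyone having to decide what caused what. A relatedness condition puts individual judgement in place of that contrast.

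Two features make the judgement fragile. First, the term intervention is not pinned down: it could mean the needle procedure, common to both periods, or the injected lidocaine. Whether an event after saline can count as related depends on which meaning is used. Second, ptosis and conjunctival flushing are visible on the face and, as markers of a successful block, are to be expected mainly after lidocaine. Anyone who sees them may guess the treatment, even with the allocation code withheld. If that person also judges relatedness, the same event could be classed differently after lidocaine and after saline.

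**Working it through.** The point is mainly textual. The plan gives no adverse event rate and no safety power, so there is no safety figure to reproduce.

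**The texts side by side**

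| Question | What the article says |
|---|---|
| Which events are collected? | All, at each assessment point (Abstract; Secondary outcomes) |
| Which events will be reported? | Those related to the intervention (Secondary outcomes) |
| Are other events excluded from the report? | Not stated; no exclusive word is used |
| Reported to whom? | Not stated |
| Who judges relatedness? | Not stated |
| Who looks for the block signs? | "another doctor, who is not involved in the operation, will observe the ptosis and conjunctival flushing" (Intervention) |
| Are assessors blind? | Declared so (Blinding; Monitoring of data quality) |
| Is a safety comparison planned? | None described |

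**Number of exposures.** The only plan figure used below is the 38 patients. It follows from the Sample size section: "With an expected difference of 10 cm/s in peak systolic velocity of the CCA between group means, an SD of 10 cm/s". A two-sided 5% two-sample t-test with 80% power (reading the printed β of 0.8 as power) needs 16.7, so 17 per group. With 10% dropout, 17 / 0.9 = 18.9, so 19 per group and 2 × 19 = 38. In the crossover this is at most 38 exposures to each treatment, or 2 × 17 = 34 if the allowed dropout occurs.

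**How a relatedness filter acts.** Let p_L and p_S be the true risks after lidocaine and saline, and a_L and a_S the shares of events called related. Then:

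reported difference = p_L × a_L − p_S × a_S

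If the true risks are equal at p, this becomes p × (a_L − a_S). All values below are assumptions, since the document supplies none.

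| True risk, both | Shares called related (lidocaine / saline) | Reported risks | Spurious difference | Expected events of 38 |
|---|---|---|---|---|
| 10% | 80% / 80% | 8% v 8% | 0 points | 3.0 v 3.0 |
| 10% | 80% / 40% | 8% v 4% | 4 points | 3.0 v 1.5 |
| 20% | 80% / 40% | 16% v 8% | 8 points | 6.1 v 3.0 |
| 30% | 80% / 40% | 24% v 12% | 12 points | 9.1 v 4.6 |
| 30% | 90% / 30% | 27% v 9% | 18 points | 10.3 v 3.4 |

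The filter costs something even when attribution is even-handed. With true risks of 20% and 10% and 80% called related in both, the report shows 16% v 8%: 8 points instead of 10.

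The table shows direction and mechanism only. The distortion is zero when a_L = a_S, and the document offers no evidence on either share.

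**The case against.** The strongest case against the point has five parts.

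- **The sentence does not say that unrelated events will be left out.** This is correct. A promise to report related events does not forbid tabulating the rest, so the exclusion is an inference. It remains the natural reading, because no other sentence covers the remaining events.
- **Reporting may mean notification, for example to an ethics committee.** The text names no recipient, so this is possible. On that reading the sentence restricts no publication, but the article then makes no commitment to publish any safety result. Either way the sentence needs clarifying.
- **No lidocaine-saline safety comparison is planned.** This is also correct. A reader might infer that a planned comparison is being biased; the article describes none. What is at stake is the contrast that the design makes available.
- **Assessors are declared blind, and roles are divided.** A reader might infer that those who attribute events will see the block signs. The document does not support that: the signs are observed by a separate doctor, and the person judging relatedness is not identified. Equally, nothing keeps that person from seeing the signs. The bias is possible, not shown.
- **Both injections count as stellate ganglion blocks in this protocol.** Haematoma and vascular trauma, listed under Expected risks, can come from the needle whichever fluid is injected, and a sensible assessor would call them related in either period. This makes strongly uneven attribution less likely for such events, but it depends on the meaning given to intervention, which the article leaves open.

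It is also fair that definitions of causality and the layout of safety tables usually belong in a full protocol or analysis plan. Their absence is not criticised here. The point concerns the reporting commitment that the article does state.

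**Conclusion.** The point holds in a limited form. The article collects all adverse events and, on its natural reading, commits to reporting only those judged related. In a saline-controlled crossover that condition is unnecessary, and it could distort the lidocaine-saline contrast if whoever judges relatedness sees the block signs.

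The size is unknown. The 4–12 point range rests on assumed risks and an assumed 80% v 40% attribution split; it is not an estimate for this trial. A reader might go further and conclude that the safety results will be biased or that events will certainly be suppressed. The document does not support either conclusion: the exclusion is inferred, the recipient is unnamed, and unblinded attribution is not shown.

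The point is minor. It does not touch the primary outcomes, the sample size or the primary analysis.

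**What to change.** Replace the reporting sentence in the Secondary outcomes section with wording such as:

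*All collected AEs and SAEs will be reported by the treatment most recently received before onset (lidocaine, saline, or none if before the first injection) and by period. Relatedness to the procedure or to the injectate will be shown as an additional classification, made without knowledge of allocation.*

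The category of none is needed because collection at each assessment point includes baseline (T0), before any injection. Tabulating by period is advisable because the observation windows may differ. If the first injection is given at enrolment, participation of 3 weeks with one week between injections leaves about 3 − 1 = 2 weeks after the second injection, against one week after the first. Naming procedure and injectate separately removes the ambiguity in the term intervention.

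If the present sentence refers to notification of an oversight body, keep it for that purpose, name the recipient, and add the sentence above for the published results.

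The cost is a longer safety table. Event collection is already planned, so the change adds no visit and leaves treatment and sample size as they are.
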